**Figure 1 figure1:**
[figure not shown]
Integrated behavioral change model (source: Hagger and Chatzisarantis [26]).

With technological advances in artificial intelligence, personalization has become easier to implement in dynamic settings, where users are interacting repeatedly with tailored components. In particular, contextual multiarmed bandits, or simply contextual bandits (CBs), have become an effective reinforcement (machine) learning personalization tool in the health behavior domain, where treatment (option) recommendations are optimally determined to maximize user performance using individual characteristics and behavior [29]. In short, CB algorithms use all available data to predict the action that would provide the best outcome to a given user, while learning from the relative performance of all possible actions. In experimental literature, there is a novel approach using CBs named adaptive interventions, emphasizing the idea that we can pose a sequential field experiment with an adaptive sampling procedure that aims to determine which types of individuals benefit from certain intervention arms over time, while also learning about the average effectiveness of each arm [30,31]. Adaptive interventions allow us to estimate the relative effectiveness of each arm while providing the optimal path for each user, based on their expected behavioral response. Overall, CBs have important advantages as an automated personalization tool, requiring less data to determine which interventions are more effective overall and allowing an understanding of which characteristics are most likely to influence individuals’ performance.

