## Methods

### Apptivate

For this project, the experiment will be conducted using the web application “Apptivate” [45], extending its initial functionally to incorporate CB algorithms connected to a routine difficulty assignment. Apptivate creates workout routines with 3 different difficulty levels, changing the total workout duration as well as rest times between exercises. PA professionals validated the routine design, ensuring that workouts match recommended guidelines for healthy adults. The overall design allows users to conduct exercises without equipment following the in-app instructions, covering different muscle groups as well as providing both warm-up and stretching exercises.

Apptivate adopts the IBC model for PA [26] as a framework for tailoring workout difficulty recommendations (ie, goals). By leveraging the IBC model, the app ensures that its recommendations address not only dynamic changes in behavior over time but also the psychological factors that influence behavior change. In particular, we capture data on the psychological constructs defined in the IBC model, which are later used as contexts for the algorithm learning process. Participants that take part in the main study will be assigned to 1 of 3 conditions:

Choice-driven: Users select their desired workout difficulty level from a predefined menu. This approach provides users with a sense of autonomy and control over their exercise routine. Choice-driven tailoring leaves the selection of the intervention to the user, allowing individuals to reveal their preferences in a participatory process [33].Data-recommended: The CB algorithm determines optimal workout difficulty (based on user data and the IBC model) and provides a recommendation to the user, but the user retains the option to choose an alternative. This design allows us to investigate the interplay between user autonomy and the effectiveness of data-driven recommendations [27].Data-driven: The CB algorithm automatically recommends workouts based on user data, including contextual features based on the IBC model, without any opportunity to opt into a different difficulty level. This method leverages a machine learning approach to personalize workout plans and potentially optimize user performance (measured as goal completion).

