### Contextual Bandits Algorithm

The contextual multiarmed bandit model used in this study is a type of reinforcement machine learning approach, which uses experimentation to learn about users’ performance and recommend the best potential option. As shown in Figure 3, the algorithm incorporates users’ past outcomes (target) and context (features) to assign probabilities to each treatment option and recommend the best possible treatment in the future (higher likelihood of success, noted in green). Once given a recommendation, users respond (either positively or negatively in this case), and this information is used for further training the algorithm for the next interaction. There are several algorithms developed to solve CB models, differing in how probabilities for each option are updated (learning) and the degree of exploration (randomness) involved in providing users with different options.

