To train the reinforcement learning algorithm for the study, initial data are required for which a pilot stage was designed. In this stage, 800 participants will be recruited at one university in order to provide 1 week of activity using the app (two 3-day rounds with a rest day in between). In order to determine the sample size for the pilot, standard power calculation was assumed with a uniform distribution over 3 arms (standard randomized controlled trial). With 665 observations, the pilot is sufficient to detect differences between users. The data from round 1 will be used to estimate the optimal arm for round 2, which will be used for calibration. Participants complete a comprehensive baseline survey eliciting the IBC model as well as several other relevant characteristics (eg, time and risk preferences; see Multimedia Appendix 1) and then are assigned randomly between the 3 difficulty levels for the first round. After completion, participants are compensated for their time. Individuals can opt out from the study at any time.

During the main part of the study, 500 participants will be recruited from multiple sites expecting to participate in a medium-term challenge, completing 10 rounds, equivalent to 39 consecutive days using the app (including rest days). As noted earlier, this provides 5000 unique examples for the algorithm to determine optimal policy over time. Users will be allocated to each arm based on their baseline survey and the trained algorithm during the pilot stage. Regardless of their initial difficulty assignment, each participant will be randomly allocated with equal probability between (1) choice-driven, (2) data-recommended, and (3) data-driven arms. Participants will be compensated for their time, and there will be additional prizes using a lottery mechanism that favors (in probability) those users completing more consecutive workout routines over the course of the study. In both the pilot and main experiment, participants will stay engaged via direct email, push notifications, and social media campaigns.

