## Results

This research is supported by the Fondecyt Initiation Grant 2024 (grant ANID 11240325; funding period 2024-2026). The pilot was conducted in September 2025. Data analysis for the pilot is undergoing, and the main study is planned for early 2026. Preliminary results from the pilot data will be available in November 2025. Our main statistical analysis includes a direct comparison (paired tests) between success rates across intervention arms, as well as by difficulty level and individual characteristics. We anticipate publishing the findings in late 2026. Dissemination will be conducted simultaneously via a web-based seminar for all participant institutions during 2026.

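### The planned comparison of success rates by difficulty level is confounded, because in the main study level is chosen, overridable or set by the algorithm rather than randomised

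*Protocol article*

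**What the plan says.** The Results section states: "Our main statistical analysis includes a direct comparison (paired tests) between success rates across intervention arms, as well as by difficulty level and individual characteristics". The words at issue are "as well as by difficulty level and individual characteristics". The section attaches no descriptive label to them and no adjustment for how the level came about.

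The Apptivate section gives three routes to a level:
- Choice-driven arm: "Users select their desired workout difficulty level from a predefined menu".
- Data-recommended arm: the algorithm "provides a recommendation to the user, but the user retains the option to choose an alternative".
- Data-driven arm: the algorithm sets the level "without any opportunity to opt into a different difficulty level".

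Under Contextual Bandits Algorithm, "the algorithm incorporates users’ past outcomes (target) and context (features) to assign probabilities to each treatment option". Under Study Design, the main-study start is described as "Users will be allocated to each arm based on their baseline survey and the trained algorithm during the pilot stage". The sentence that follows it refers to an initial difficulty assignment and randomises the three conditions with equal probability regardless of it, so the arms in this quote are difficulty levels. Random assignment of levels is described only for the first round of the pilot.

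The Statistical Analysis section puts the primary analysis on conditional average treatment effects per intervention arm, with mixed-effects models for repeated measures and unspecified sensitivity analyses. Weighting by assignment probability is not mentioned anywhere in the article.

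**The concern.** Level is a post-randomisation variable tied to predictors of success. The Introduction itself says that preferred intensity and physical capability vary widely between people. If abler users tend to do harder workouts, by choice or because the algorithm sends them there, hard workouts collect the users who would complete anything, and the success rate for that level rises for reasons unrelated to the level. If the sentence instead means comparing conditions within a level, it conditions on the same variable and gives up the balance that randomisation bought.

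A second problem arises without self-selection. When a bandit sees a poor early run for one level it samples that level less, so the low early mean is not corrected. Plain sample means are then biased downward, most of all for the least-used level.

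At stake is what the trial says about which level suits which user, which the second objective touches through adherence to set goals. A crude rate could show hard workouts as completable as easy ones, or more so.

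**Working it through.** The article gives no completion rates, effect sizes or selection strengths. Its only related figure is 500 participants × 10 rounds = 5000 examples, which checks but does not bear on this point. All rates below are assumptions. Gaps are easy minus hard, in percentage points.

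**1. Two-type formula.** Half the users are fitter and half less fit. Their success rates on the easy level are pF and pU, the hard level costs both types d, and s = P(hard | fitter) = P(easy | less fit).

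Easy rate = (1−s)·pF + s·pU. Hard rate = s·(pF−d) + (1−s)·(pU−d).

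Crude gap = d − (2s−1)(pF−pU).

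With d = 10 points:

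| pF / pU | s=0.5 | 0.6 | 0.7 | 0.8 | 0.9 |
|---|---|---|---|---|---|
| 0.80 / 0.50 | +10 | +4 | −2 | −8 | −14 |
| 0.75 / 0.55 | +10 | +6 | +2 | −2 | −6 |
| 0.70 / 0.60 | +10 | +8 | +6 | +4 | +2 |

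For example, at 0.80/0.50 and s = 0.7: 10 − 0.4 × 30 = −2. The sign reverses when (2s−1)(pF−pU) > d. Comparing within user type returns +10 for every s.

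**2. Three levels, self-selected.** Logit success = ability + (1.0, 0.4, −0.2), ability SD 1. True success is about 70/58/46%, a gap of 24. Level is chosen by multinomial logit with slope 0.5, 1 or 1.5 on ability; 10 rounds for the repeated-measures rows.

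| Analysis | slope 0.5 | 1 | 1.5 |
|---|---|---|---|
| Crude pooled | +7 | −2 | −7 |
| Random-intercept logistic | +18 | +10 | +4 |
| Paired within person, stable ability | +25 | +25 | +27 |
| Paired within person, plus day-to-day ability (SD 1 logit) that also drives choice | +6 | −3 | −8 |

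The paired rows use only users who did both the easy and the hard level: about 440, 350 and 280 of 500 under stable ability. In the last row the true gap is about 21, the same logit shifts averaged over a total ability SD of √2.

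**3. All three arms.** 501 users, 10 rounds, ability SD 1 logit, harder levels going to abler users in every arm. With random levels the gap is about +16. Pooled over arms it is +8, 0, −9 and −18 at selection correlations of 0.2, 0.4, 0.6 and 0.8. At 0.6 it is reversed in each arm: −10 choice-driven, −8 data-recommended, −8 data-driven. With ability SD 0.5 the pooled gap runs from +18 with no selection to −1 at 0.8; with SD 1.5, from +14 to −32.

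**4. Adaptive sampling alone.** Three equal levels at 65%, 167 users, 10 rounds, batched epsilon-greedy with epsilon 0.1, 4000 replicates. Naive level means average about 1.6 points too low, and the least-used level about 3.6 points too low (3.5 on a rerun).

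**The case against.** The strongest reply is that the plan says paired tests. Participants complete 10 rounds and can do several levels, so a paired test by level is most naturally within-person, and this removes the stable-ability confounding behind the crude reversal. The participant effect in the mixed model removes part of it too. Both points stand, as the table shows. But pairing handles only what is constant within a person. The protocol's rationale is that context changes over time and affects completion, and the algorithm reacts to past outcomes. Once day-to-day ability drives the choice, the paired gap moves nearly as far from the truth as the crude one. The sentence also does not say what is paired.

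A reader might infer that the article's claim of robust causal inference falls with the level comparison. It does not: that claim concerns choice versus autonomy, which is the randomised comparison of the three conditions. Comparisons by baseline characteristics are likewise unaffected. The Introduction's sentence "Adaptive interventions allow us to estimate the relative effectiveness of each arm while providing the optimal path for each user" is a general statement about such designs, not an analysis rule.

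It is fair, too, that epsilon-greedy is named only for the sample-size simulations, with the trial algorithm to be picked from the pilot, so the adaptive-bias figures are conditional on that rule. Weighting details can belong in an analysis plan not shown here. What is not an omission is that the article commits the main analysis to a direct comparison by level.

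**Conclusion.** The point holds for the by-level comparison and only there. As written, it would not estimate the effect of a difficulty level.

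The direction and size depend on assumptions. Under the rates used here, a crude comparison turns a 24-point gap into anything from +7 to −7. Within-person pairing is close to right if ability is stable, and can shrink or reverse the gap if selection varies over time. Weak selection or similar users only attenuate it. A reader might take reversal as the expected result; the documents do not support that, since they give neither success rates nor selection strengths, and the simulations assume that abler users get harder levels. The adaptive-sampling part is smaller, about 1.6 points on average and 3.6 for the least-used level.

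Level comparisons in pilot round 1 are randomised and free of this problem.

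**What to change.** Before the main study starts:

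1. Label by-level success rates from user-chosen rounds as descriptive, and say what the paired tests pair.
2. Estimate level effects from pilot round 1, where levels are randomised (one university, one 3-day round), and from algorithm-assigned rounds in the data-driven arm.
3. Log the assignment probability of every level at each decision, including the starting level, and state a floor below which none may fall. Use inverse-probability or augmented inverse-probability estimates, with a variance suited to adaptively collected data.
4. In the data-recommended arm, analyse by the level recommended, with the same weighting, and not by the level done.

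The cost is one logged field per decision, wider intervals for rarely assigned levels and a small loss from exploration. The weighted estimators were not simulated here. The logging has to be in place at launch: without saved probabilities, or with some at zero, design-based weighting may not be recoverable afterwards.

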## Discussion

### Anticipated Findings

This study introduces a novel approach to promoting sustained PA through a mobile app, leveraging CB learning for personalized goal difficulty recommendations, under an IBC framework. By combining this theory-informed machine learning approach with different levels of user autonomy, the intervention addresses critical gaps in existing mHealth literature, particularly the role of autonomy and motivation on personalized goal setting. We expect to find heterogeneity in both (1) individual behavioral responses to personalized goals, and (2) autonomy preferences for choice versus automation. Such heterogeneity should align with the IBC model and reflect the particular hurdles of motivation versus goal difficulty.

Findings from this field experiment will contribute to the growing field of adaptive digital health technologies, offering practical insights for scaling effective interventions for sustained health behavior. Ultimately, this research has the potential to inform public health strategies by providing evidence on the interplay between user autonomy and data-driven recommendations, fostering more engaging and effective health behavior change digital tools.

There are limitations to this study. First, participant dropout may introduce bias if attrition is nonrandom, reducing overall statistical power. Our sample size considers a maximum 20% dropout rate, to maintain statistical validity. Second, findings may not generalize to populations of different ages or health statuses or to those without smartphone access and from other cultural contexts beyond those included in the study. In an effort to provide better external validity, we aim to implement this study in countries with different languages and cultural backgrounds.

### Conclusions

PA maintenance is key to achieving long term health goals. Tailored digital interventions are promising strategies for PA adherence, but personalization often fails to consider dynamic contextual changes. The proposed protocol for a PA intervention using adaptive experimentation can provide robust causal inference on the role of choice versus autonomy when tailoring goal difficulty is done under an adaptive data-driven approach. Dissemination plans will focus both on participants and the scientific community, and all participatory events are designed to be conducted simultaneously via a web-based seminar for all participant institutions during 2026.

## Appendix

Multimedia Appendix 1 Baseline questionnaire.

Multimedia Appendix 2 SPIRIT 2025 checklist of items to address in a randomized trial protocol.

Multimedia Appendix 3 Peer review report by INTERTRANSDISCIPLINARY Evaluation Group, FONDECYT, Agencia Nacional de Investigación y Desarrollo, (ANID; National Agency for Research and Development, Chile).

## Abbreviations

CB: contextual bandit
IBC: Integrated Behavior Change
mHealth: mobile health
PA: physical activity
SPIRIT: Standard Protocol Items: Recommendations for Interventional Trials
